## Methods/Design

### Study design

The study is a three-armed prospective randomised controlled trial targeting approximately 420 males and females aged 18 years or older and living predominantly in the state of Queensland. An online intervention was considered to be potentially useful in this geographical area given that Queensland is a state where access to services is limited in regional and rural areas. Consenting participants will be randomised in a 200:200:20 ratio to (a) the intervention or (b) information only or (c) a control group using a computer-generated random number sequence. Randomisation will be undertaken by the consultant project web developers in association with the project investigator. Participants in each of the groups will complete three online assessments; at baseline, one week, and one month after the initial survey. Participants randomised to the intervention and information only groups will complete a brief survey immediately following completion of their respective conditions to measure each of the main study constructs.

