Computer-based interventions have been used to target behaviour change in a wide range of health issues over the last decade and provide a means of administering economical and easily accessible interactive health interventions which are far reaching within the population [13,34]. Research by Cugelman et al. [34] found that, compared with waitlists, online interventions have demonstrated moderate efficacy while, compared with print materials, they offer similar impacts but with the advantages of lower costs and broader reach. Further, research by Webb et al. [35] found that more extensive use of theory, and specifically online interventions based on the TPB, tended to have more substantial effects on behaviour. Despite their demonstrated efficacy in producing health behaviour change, online, multi-behavioural, theory-based interventions have yet to be explored fully as a medium to target adults’ sun-protective attitudes, beliefs, and sun-protective behaviour within the Australian context.

Limited research has examined the efficacy of online/web-based interventions in increasing a specific sun-protective behaviour (e.g., sunscreen use; [36]); however, there is a particular dearth of theory-based, online interventions targeting multiple sun-protective behaviours. We hypothesise that adults exposed to the online intervention will report an increase in positive sun-protective attitudes, normative support, and self-perceptions of control/self-efficacy, leading to increased sun protection intentions and behaviour, compared with participants in both an information only and control group (measurement only).

This paper presents the study protocol for an online intervention aimed at improving sun-protective behaviour in adults. The research will use an extended version of the TPB to develop and test the efficacy of an online sun-protective intervention derived from this approach. The intervention will target previously identified attitudes toward sun protection, normative influences, and barriers and motivators, as well as targeted aspects of personal choice/responsibility, and tanning being part of Australian identity.

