#### Sample size

It is aimed to recruit a total of 420 participants (200 intervention/200 information only/20 control). Based on our previous research in the area, it is anticipated that there will be approximately 35% attrition over 4 weeks of follow-up for reasons such as failure to complete follow-up questionnaires. A total sample of approximately 260 (420–140) completing participants (130/group) is required to detect a medium effect in sun-protective behaviour. This sample size was determined by power analysis using the G*Power program [37,38]. Significance level (alpha) was established at 0.05 to avoid a Type 1 error, power (1–beta) was set at 95% to avoid a Type II error, and effect size was determined at .25. Therefore, for a 95% chance of detecting as significant a 4 week difference in sun safe behaviour, approximately 130 participants in each group are needed to complete the study.

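### The hypothesis names the control arm as a comparator, but the sample size covers only intervention versus information only and does not say so; about 13 control completers leave that contrast with low power

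*Protocol article*

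**What the plan says.** Three statements in the protocol article bear on this.

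- **Hypothesis (end of the Background).** Adults given the online intervention are expected to improve "compared with participants in both an information only and control group (measurement only"). Both comparators are named, with no ranking between them.
- **Allocation (Study design; repeated under Sample size).** "Consenting participants will be randomised in a 200:200:20 ratio to (a) the intervention or (b) information only or (c) a control group".
- **Sample size.** "Significance level (alpha) was established at 0.05", "power (1–beta) was set at 95% to avoid a Type II error" and "effect size was determined at .25", which the text calls a medium effect. About 35% attrition is expected over four weeks. The requirement is about 260 completers in total, and the section concludes that "approximately 130 participants in each group are needed to complete the study".

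The Data analyses section plans general linear models on the change outcomes with group, time and their interaction. It neither restricts nor describes the role of the control arm. No section calls that arm descriptive, exploratory or a check on measurement effects.

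**The concern.** A reader who takes the hypothesis and the Sample size section together will assume that the 95% power and the 130 completers per group apply to every comparison in the hypothesis. The control arm randomises 20 people, so it could not supply 130 completers even with no attrition.

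Two things are at stake. A non-significant intervention-versus-control result could be read as absence of effect when the contrast was simply imprecise. And if the intervention and information only work about equally well and both beat doing nothing, the trial would have a low chance of showing it.

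**Working it through.** **Inputs from the Sample size and Study design sections.** Alpha 0.05; power 95%; effect size .25; attrition 35%; allocation 200:200:20.

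**Assumptions, because the article does not state them.** The effect size is Cohen's f, so d = 2f = 0.5 for two groups; the label medium supports this. The test is two-sided. No baseline adjustment is made in the base case. Each assumption is varied below.

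**1. Completers.** 200 × 0.65 = 130 in each large arm and 20 × 0.65 = 13 in control. In reverse, 130 / 0.65 = 200, which reproduces the size of the large arms.

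**2. The plan's own figure.** With f = .25, alpha 0.05 and 95% power, one-way ANOVA needs 210 completers (105 per group) for two groups, or 252 (84 per group) for three equal groups. Neither is exactly 260 at 130 per group. But 260 = 2 × 130 = 400 × 0.65, so the total has no room for a third arm.

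**3. Power of each comparison.** The standard error in SD units is √(1/n₁ + 1/n₂), the noncentrality is d divided by that, and power comes from the noncentral t distribution.

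| Comparison | SE | Noncentrality at d = 0.5 | Power |
|---|---|---|---|
| Intervention v information only, 130 v 130 | √(2/130) = 0.124 | 4.03 | 98.0% |
| Intervention v control, 130 v 13 | √(11/130) = 0.291 | 1.72 | 40.0% |

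The standard error against control is √(11/2) = 2.35 times larger. The 95% confidence interval half-width is about 0.58 SD, against 0.24 SD for the other comparison. The detectable difference against control, unadjusted, is d = 0.82 at 80% power and d = 1.06 at 95%.

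**4. Sensitivity of the 40%.**

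| Variant | Power v control |
|---|---|
| .25 read as d, two-sided | 13.7% |
| One-sided 5%, d = 0.5 | 52.6% |
| No attrition, 200 v 20 | 56.5% |
| Both active arms pooled, 260 v 13 | 41.8% |
| Baseline as covariate, assumed correlation 0.5 / 0.7 / 0.8: d / √(1 − ρ²) | 50% / 67% / 81% |
| Change scores, same correlations: d / √(2(1 − ρ)) | 40% / 60% / 77% |

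None reaches 95%. For covariate adjustment to do so, √(1 − ρ²) would have to fall to 0.5 / 1.06 = 0.47, a baseline correlation of about 0.88. The article gives no correlation.

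**5. What control would need.** With 130 intervention completers and d = 0.5, 95% power needs 88 control completers (88 / 0.65, so 136 randomised), and 80% power needs 43 (67 randomised). Supplying 130 completers in all three arms would take 3 × 200 = 600 randomised.

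**The case against.** The strongest reply is that the 95% was meant for the two large arms only. The arithmetic supports that: 260 is twice 130, and the comparison so sized has ample power. The article never attaches the 95% to the control contrast, so a reader who infers that it claims 95% there goes beyond the text. What remains is that the scope is unstated while the hypothesis names control on equal terms.

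Second, 40% is one scenario. The planned models use change from baseline, which may raise power. Also, if d = 0.5 holds against information only and that material itself does some good, the effect against control exceeds 0.5: illustrative values of 0.6, 0.7 and 0.8 give 54%, 67% and 78%. This stands as a reason to give a range. It does not bring the contrast to the stated 95%.

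Three stronger readings are tempting and are not supported:

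- **That both comparisons must be significant for the trial to succeed.** The hypothesis is a narrative statement, and the Data analyses section sets no such rule. A joint power figure would test a criterion the plan does not contain.
- **That little difference is expected against information only, so the arms are sized the wrong way round.** The Background does report that "compared with waitlists, online interventions have demonstrated moderate efficacy while, compared with print materials, they offer similar impacts". That concerns online interventions in general against print, whereas the information arm here is an online video plus fact sheets. The next sentence says that theory-based online interventions, those using this trial's theory in particular, tended to do better.
- **That the trial cannot show a benefit over control.** Power is low, not nil.

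**Conclusion.** The point holds as an inconsistency of scope. The hypothesis covers two comparisons and the sample size covers one, without saying so. The requirement of 130 completers per group is unmet for control by a wide margin (about 13). Intervention versus information only is adequately sized: about 98% at d = 0.5, two-sided.

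Intervention versus control has about 40% power on the same assumptions. The range is about 14% to 81% across the readings of the effect size, sidedness and baseline adjustment that were tried. The exact figure rests on those assumptions. The conclusion that this contrast falls short of 95% holds in every variant tried and would change only with a much larger effect or a very high baseline correlation. The main comparison is not undermined.

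**What to change.** Wording changes, with no effect on recruitment or randomisation:

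1. **Sample size section:** state that the 95% power and the 130 completers per group apply to intervention versus information only. Name the effect-size metric and the sidedness of the test.
2. **Hypothesis in the Background:** limit the confirmatory claim to intervention versus information only, and state what the control arm is for.
3. **Data analyses section:** report control contrasts as estimates with 95% confidence intervals. Give their power with its assumptions (about 40% at d = 0.5, two-sided, unadjusted), and say that a non-significant control contrast will not be read as no effect.

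The cost is that the trial makes no confirmatory claim against a no-intervention control.

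If the sponsor wants such a claim, the same 420 could be reallocated. For example, 170:170:80 gives about 110, 110 and 52 completers, with about 96% power against information only and 84% against control at d = 0.5. This is a trade-off for the sponsor to weigh, not a required change: no arm would then reach 130 completers, and the control contrast would still be below 95%.

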### Study aim

The aim of this study is to evaluate the effectiveness of a TPB-based online sun safety intervention in increasing positive attitudes, normative support, and perceptions of self-efficacy/control, leading to increased sun protection intentions and behaviour in adults.

### Study sample

#### Sample eligibility criteria and recruitment procedures

Eligibility criteria will include male and female adults (aged 18 or over) living in Australia. Participants will be recruited from the community through university-based media releases, community billboards, newsletters, email lists, snowball sampling techniques, and the use of an existing database of participants from a previous sun safety study who consented to be contacted for participation in future studies.

Participants will receive an email and flyer providing information about the study and a link to the study website. Consent to participate will be obtained after participants are presented with a comprehensive outline of the study online and will involve participants clicking a box indicating that they agree to participate in the study. Participants will be randomised to a study condition immediately after completing Questionnaire 1. A link to the post-intervention questionnaires will be emailed to participants a week and then one month after the initial questionnaire.

Participants are advised that they will be eligible to receive an AUD $20 store voucher after completion of Questionnaire 1 and another AUD $20 store voucher after completing the two follow up questionnaires 1 week and 1 month later.

#### Sample size

It is aimed to recruit a total of 420 participants (200 intervention/200 information only/20 control). Based on our previous research in the area, it is anticipated that there will be approximately 35% attrition over 4 weeks of follow-up for reasons such as failure to complete follow-up questionnaires. A total sample of approximately 260 (420–140) completing participants (130/group) is required to detect a medium effect in sun-protective behaviour. This sample size was determined by power analysis using the G*Power program [37,38]. Significance level (alpha) was established at 0.05 to avoid a Type 1 error, power (1–beta) was set at 95% to avoid a Type II error, and effect size was determined at .25. Therefore, for a 95% chance of detecting as significant a 4 week difference in sun safe behaviour, approximately 130 participants in each group are needed to complete the study.

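### The sample-size figures do not agree with one another: 420–140 is 280, not 260, and for two groups at Cohen's f = .25 the stated 95% power needs 105 completers per group, not 130.

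*Protocol article*

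**What the plan says.** All the figures stand in the Sample size section of the protocol article.

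- Recruitment: "It is aimed to recruit a total of 420 participants (200 intervention/200 information only/20 control"). The Study design section agrees: "Consenting participants will be randomised in a 200:200:20 ratio".
- Loss to follow-up: "it is anticipated that there will be approximately 35% attrition over 4 weeks of follow-up".
- Requirement: "A total sample of approximately 260 (420–140) completing participants (130/group) is required to detect a medium effect in sun-protective behaviour".
- Inputs: "Significance level (alpha) was established at 0.05 to avoid a Type 1 error"; "power (1–beta) was set at 95% to avoid a Type II error"; "effect size was determined at .25".

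The section ends by saying that about 130 completers in each group are needed for a 95% chance of detecting a difference in behaviour at four weeks. G*Power is named as the software. The effect-size metric, the test, the number of groups compared and the sidedness are not given.

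**The concern.** Two things do not fit. First, the subtraction in brackets does not give the number beside it. It starts from a total that includes the control arm and ends at a total that leaves it out.

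Second, a total of 260 made up of 130 per group describes two groups, but two groups of 130 do not give 95% power at .25 when .25 is read as Cohen's f.

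This paragraph is the only justification the article gives for the trial's size. A reader who wants to know what effect the trial could detect, and in which comparison, cannot recover that from the printed figures. The Background hypothesises superiority over both the information-only group and the control group. A statement of 95% power with 130 in each group could therefore be taken to cover the control comparison as well, where only about 13 completers are expected.

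**Working it through.** **Inputs.** From the Sample size section: 200/200/20 recruited, 35% attrition, alpha 0.05, power 95%, effect size .25, 260 completers, 130 per group. Assumed because not stated: two-sided t tests, and .25 as Cohen's f. For two equal groups d = 2f, so f = .25 is d = .50.

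**1. The plan's own counts**

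- As printed: 420 – 140 = 280.
- 35% of all three arms: 0.35 × 420 = 147, and 420 – 147 = 273. By arm: 200 × 0.65 = 130, 200 × 0.65 = 130, 20 × 0.65 = 13.
- 35% of the two large arms: 0.35 × 400 = 140, and 400 – 140 = 260, which is 130 per group.

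So 140, 260 and 130 per group all belong to the 400 in the two large arms. Only the 420 is out of place.

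**2. Two groups of 130, f = .25 (d = .50)**

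Noncentrality of the t test: δ = d / √(1/n₁ + 1/n₂) = 0.50 / √(2/130) = 4.03, on 258 degrees of freedom, with a two-sided critical value of 1.969. Power is 98.0%.

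Smallest n for 95%:

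| n per group | δ | Power |
|---|---|---|
| 104 | 3.606 | 94.8% |
| 105 | 3.623 | 95.0% |
| 130 | 4.031 | 98.0% |

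The requirement is therefore 105 per group (210 in total). Turned round, 130 per group has 95% power for d = 0.45, or f = 0.22.

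**3. Where could 95% at about 260 come from?**

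Omnibus F test with 2 numerator degrees of freedom, f = .25, λ = f²N:

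- N = 260: λ = 0.0625 × 260 = 16.25; power 95.7%.
- N = 252 (84 in each of three equal groups): λ = 15.75; power 95.1%. The threshold is crossed at N = 251.
- Three groups of 130 (N = 390): λ = 24.4; power 99.6%.

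A three-group F test thus gives 95% at a total close to 260, but as 84 per group, not 130. The planned completers are 130/130/13, not three equal groups.

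Two groups of 130 also come near 95% with a Bonferroni alpha (96.2% at 0.025, 94.7% at 0.0167), but the section states 0.05 and mentions no adjustment.

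**4. The control comparison**

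130 v 13 at d = .50: δ = 0.50 / √(1/130 + 1/13) = 1.72, on 141 degrees of freedom; power is about 40%.

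**5. The other metric, for completeness**

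If .25 were a standardised mean difference, 130 v 130 would give δ = 0.25 / √(2/130) = 2.02 and power 51.9%, and 95% would need 417 per group.

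**The case against.** The strongest defence is that 95% does follow from a standard calculation. The trial has three arms, and the Data analyses section plans general linear models with group and group-by-time terms. A 2-df F test at f = .25 gives 95.7% at a total of 260. This stands: it would be wrong to say that the stated power can never be obtained. It does not rescue the text, because that calculation asks for 84 in each of three equal groups, while the section says 130 per group. That 260 began as a three-group total is in any case an inference, since no test is named.

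A second defence is that the subtraction slip changes nothing downstream. This also stands: with 400 in place of 420, the attrition rate, the 260, the 130 per group and the 200/200 recruitment all agree.

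A third is that an article may leave the test family and other software inputs to the full protocol. Their absence alone would indeed be no finding. The point here is that the figures the article chose to print do not fit together.

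A reader might infer from the unstated metric that the trial is badly underpowered, at about 52%. The document does not support that. The section calls the effect medium, which fits .25 as Cohen's f and not as a standardised mean difference. On the f reading, intervention v information only has more power than claimed.

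**Conclusion.** The point holds as an inconsistency in the planning figures, of minor to moderate severity. The subtraction is wrong as printed: 280, not 260. The requirement is wrong for the two-group comparison that the wording describes: 105 per group for 95% power, with 130 per group giving about 98%. The stated 95% at a total near 260 matches a three-group omnibus test that has neither 130 per group nor the planned split.

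These figures assume a two-sided alpha of .05 and .25 as Cohen's f. No shortfall is shown for the main contrast. The stated power should not be extended to comparisons with control, where it is about 40% at the same effect size.

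**What to change.** In the Sample size section:

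1. Change 420–140 to 400–140.
2. State that .25 is Cohen's f, and name the test, its sidedness and the number of groups. The sponsor should confirm these from the G*Power record.
3. If the comparison meant is intervention v information only, restate as follows: with f = .25 (d = .50) and two-sided alpha .05, 105 completers per group give 95% power; 200 randomised per group with 35% attrition leave about 130, which gives about 98% power, or 95% power for d of about 0.45. If a three-group test was meant, give its requirement (252 in total, 84 in each of three equal groups) and explain how it applies to an expected 130/130/13.
4. State that the 20 controls (about 13 completers) are outside a two-group calculation and that the stated power does not cover comparisons with control.

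The cost is wording only. Recruitment stays at 200/200/20.

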### Study conditions

#### Intervention

The intervention is computer-based and will be conducted in the participants’ homes or in their chosen location based on accessibility to the online intervention. The single session interactive intervention will take approximately 20-25 minutes to complete and will address three main constructs related to sun protection.

The first construct, sun protection-related attitudes and beliefs, will be targeted through a series of questions and quizzes in which participants will be asked to consider advantages and disadvantages of sun protection as well as common misconceptions about sun protection. The second construct, fostering perceptions of friendship group normative support for sun protection, will be addressed through the use of animated scenarios depicting situations in which a character is faced with opposition to performing sun-protective behaviour from an important referent or referents. A series of questions will prompt participants to consider how they would respond in each situation and how they could prevent the situation from occurring. An increase in perceptions of control/self-efficacy with using sun protection is the third construct addressed in the intervention and is addressed by a set of animated scenarios and accompanying questions which ask participants to consider specific barriers to sun-protective behaviour and to suggest solutions to these barriers. Additionally, participants will be prompted to set a specific sun safe goal, to identify barriers to success, and to propose solutions to the barriers. Participants will be asked to create a contract online which outlines their intentions to overcome these barriers and will be provided with an option to print/save or email the contract to a friend. Further to these constructs, participants will be prompted in the intervention to consider their attitudes to tanning (including culturally-based as an Australian) and issues related to personal responsibility to engage in sun protection.

